### Health-economic evaluation

2.8

We will conduct a within-trial health economic evaluation (41) whereby outcome and cost data will be compared at week 11. It will encompass two analyses: (1) a cost-effectiveness analysis using the responder status as outcome; (2) a cost-utility analysis using the outcome quality adjusted life years (QALYs) measured using the AQOL-6D (30).

Health-related quality of life (HRQoL) will be collected using the AQOL-6D (28, 42), a multi-attribute utility instrument for use in economic evaluations. Data on resource use will be collected using an adapted version of the self-reported Treatment Inventory of Costs in Psychiatric Patients (TIC-P) questionnaire (36). Costs will be measured from three perspectives: a healthcare organization payer perspective (including intervention costs only), a healthcare system perspective (additionally including costs related to the use of medical resources, and medication), and a societal perspective (additionally including social care costs and productivity losses for the individual). Costs from each perspective will be analysed in relation to clinical efficacy (responder status; cost-effectiveness analysis) and QALYs (cost-utility analysis). Results will be presented as incremental cost-effectiveness ratios (ICER), as the ratio between the difference in costs and the difference in health outcomes ICERs will be put against values of willingness to pay for a QALY to determine cost-effectiveness.

Standard health economic evaluation techniques will be used to explore uncertainty around the cost and effect data, which will be represented on cost-effectiveness planes. The probability of cost-effectiveness according to different willingness to pay thresholds will be represented on cost effectiveness acceptability curves (43).

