The primary aim of the study is to investigate whether guided internet-delivered ERP-based BT is superior to an active control condition consisting of guided internet-delivered general psychological support in reducing TS/CTD symptoms. We hypothesize that, compared to the control group, participants in the treatment group will show greater reduction in tic severity, as measured with Yale Global Tic Severity Scale - Total Tic Severity subscale (YGTSS-TTS) (22) at the primary endpoint (post treatment or week 11 after treatment start).

The secondary aim at the primary endpoint (week 11 after the start of the treatment) is to compare the two arms regarding:
(1)Tic-related impairment(2)Rates of responders(3)Self-rated tic severity(4)Symptoms of depression(5)Quality of life(6)Cost-effectivenessThe third aim is to evaluate long-term maintenance of gains. We hypothesize that the intervention condition will be superior to the control condition at week 23 after the treatment start (better response, less severe symptoms, higher quality of life) regarding all outcome measures and that the results will be maintained in the intervention group at the 14-month follow-up. The fourth aim is to evaluate the cost-effectiveness of the intervention from the healthcare organization payer perspective, the healthcare system perspective, and the societal perspective.

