#### Intervention condition: internet-delivered exposure with response prevention

2.3.1

The active intervention will contain eight chapters with homework assignments after each chapter, as well as working sheets for the participants to register and monitor their activity during the treatment. The participants will work with their treatment for 10 weeks, communicating with their therapists via asynchronous written messages in the platform. On the first day of the treatment, the participants in both intervention and control conditions will be greeted by their therapist via a message sent on the treatment platform. The therapists will introduce themselves, inform the participants about the outline of the treatment, and encourage them to start working with the treatment content immediately. The first two chapters of the treatment will be available to the participants from the start. The participants will be encouraged to work with one treatment chapter per week and the following chapter will be opened by the therapist when the previous week's homework is reviewed. The therapist's role will be to encourage the participants’ activity in the treatment and follow up on inactivity, problem solve and follow up on potential safety issues when necessary.

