#### Control condition: internet-delivered general psychological support

2.3.2

Participants who are randomized to the control group will receive access to brief psychoeducational content about TS/CTD in the platform in combination with general psychological support from a therapist. The materials will be divided in two chapters. Chapter 1 will cover the topics of what tics are, and the different ways stress can influence the symptoms. Chapter 2 will focus on supporting stress management and healthy lifestyle habits related to food, sleep, and physical activity. No active BT components (i.e., ERP, HRT, applied relaxation) are provided to the participants in the control group. The therapists will welcome the participants to the treatment, encourage them to engage in the treatment content and to reach out to the therapist if they have any questions. Thereafter, the therapists will only reply to the participants’ messages without taking any contact initiative themselves (unless there is an indication of severe deterioration or severe depressive symptoms or suicidal ideation requiring medical attention). The aim of the control condition is to control for basic therapist attention, relevant disorder-specific content, and the passage of time. The participants in the control group who wish to have additional help will have an opportunity to receive I-BT after the data from the first long-term follow-up (week 23 after the start of the treatment) are collected.

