### Outcomes

2.4

If not specified otherwise, the outcome measures will be collected at pre-treatment, at week 11 counting from the start of the treatment (post-treatment, primary endpoint), week 23 (3 months after the end of the treatment), and 14 months after the treatment start (12 months after the end of the treatment) (Table 3).

**Table 3 T3:** Overview of the recruitment, treatment, and assessment points and measures.

	Enrolment	Allocation	Pre-treatment	Week 1–3	Week 4–7	Week 8–10	Week 11 (post-treatment, primary endpoint)	Week 23	14-month follow-up
Enrolment									
Eligibility screen	X								
Informed consent	X								
Allocation		X							
Treatment									
ERP				X	X	X			
Control condition				X	X	X			
Clinician-administered measures									
DSM-5 criteria for TS/CTD	X								
SCID-5	X								
MINI	X								
YGTSS	X						X	X	X
CGI-S	X						X	X	X
CGI-I							X	X	X
iiPAS					X		X		
Self-rated measures									
ATQ1	X		X	X	X	X	X	X	X
RAADS-14			X						
ASRS			X						
PUTS			X						
MADRS-S^b^	X		X	X	X		X	X	X
AUDIT	X								
DUDIT	X								
WSAS^a^			X	X	X	X	X	X	X
GTS-QoL			X				X	X	X
AQoL-6D			X				X	X	X
TIC-P			X				X	X	X
Negative effects							X	X	
Other adverse events				X	X		X	X	
CEQ					X				
WAI-SR					X				
Time spent on the programme^a^				X	X	X	X	X	X

AQoL-6D, assessment of quality of life—6 dimensions; ASRS, adult ADHD self-report scale; ATQ, adult tic questionnaire; AUDIT, alcohol use disorders identification test; CEQ, credibility and expectancy questionnaire; CGI-I, clinical general impression—improvement; CGI-S, clinical general impression—severity; DUDIT, drug use disorders identification test; ERP, exposure with response prevention; GTS-QoL, gilles de la Tourette syndrome—quality of life scale; iiPAS, internet interventions patient adherence scale; MADRS-S, montgomery—asberg depression rating scale—self-rated; MINI, the mini international neuropsychiatric interview; PUTS, premonitory urge for tics scale; RAADS-14, ritvo autism and asperger diagnostic scale; SCID-5, OCD and related disorders section of the Structured Clinical Interview for DSM-5; TIC-P, treatment inventory of costs in patients with psychiatric disorders; TS/CTD, Tourette syndrome/chronic tic disorder; WAI-SR, working alliance inventory—self-rated; WSAS, work and social adjustment scale.

^a^
Administered weekly during the 10-week treatment.

^b^
Administered at week 3 and 7.

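### The cost-utility analysis stops at week 11, although costs and utilities up to week 23 are collected before controls are offered I-BT

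*Protocol article*

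**What the plan says.** Section 2.8 (Health-economic evaluation) describes a within-trial evaluation in which "outcome and cost data will be compared at week 11". It has two parts: a cost-effectiveness analysis on responder status, and "a cost-utility analysis using the outcome quality adjusted life years (QALYs) measured using the AQOL-6D". Each is costed from three perspectives, the narrowest being "a healthcare organization payer perspective (including intervention costs only". The resulting ratios are to be judged against willingness to pay for a QALY.

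Four other places bear on the horizon:

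- **Treatment length (section 2.3.1).** "The participants will work with their treatment for 10 weeks". Table 3 shows both conditions running over weeks 1 to 10.
- **Data collection (section 2.4 and Table 3).** After the week-11 assessment, outcomes are collected at "week 23 (3 months after the end of the treatment), and 14 months after the treatment start". Table 3 marks AQoL-6D and TIC-P at pre-treatment, week 11, week 23 and 14 months.
- **Access for controls (section 2.3.2).** Control participants "will have an opportunity to receive I-BT after the data from the first long-term follow-up", which is the week-23 assessment.
- **Aims (Introduction).** Cost-effectiveness is listed among the week-11 secondary aims. The third aim reads "We hypothesize that the intervention condition will be superior to the control condition at week 23 after the treatment start", and higher quality of life is part of that hypothesis. A fourth aim covers cost-effectiveness from three perspectives and gives no time limit.

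**The concern.** QALYs accrue with time, whereas the cost of a 10-week programme is spent by the end of treatment. Stopping the count at week 11 therefore takes in nearly all of the intervention cost but only the period in which any benefit is building up. The trial itself expects a quality-of-life advantage twelve weeks later and collects the data to show it. Up to week 23 no control participant has been offered I-BT by the trial, so a randomised comparison of costs and QALYs over that longer period is available without further data collection.

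At stake is the comparison with willingness to pay. The same programme with the same effect could fall on different sides of a threshold according to whether the count stops at week 11 or week 23, and the plan reports only the former.

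**Working it through.** The article gives no QALY, cost or cost-per-QALY figure, so there is no stated result to reproduce. The check asks how far the choice of horizon alone moves the answer.

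**Inputs from the article**
- Horizon: week 11 (section 2.8).
- Programme length: 10 weeks (section 2.3.1), so the intervention cost is essentially complete at week 11.
- AQoL-6D at pre-treatment, week 11 and week 23 (Table 3).
- No I-BT offered to controls before the week-23 data are collected (section 2.3.2).

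**Assumptions**
- The utility difference between arms is 0 at baseline and rises linearly to D at week 11. AQoL-6D is not measured in between, so a straight line is what an area-under-the-curve calculation on these data would use.
- At week 23 the difference is r × D, reached linearly, with r from 0 (faded to nothing) to 1 (fully kept).
- D and the incremental intervention cost are not given in the article. Both cancel in the ratios.

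**Formulas (trapezoids, weeks divided by 52)**
- Gain to week 11 = ½ × D × 11/52 = 0.106 D.
- Gain to week 23 = 0.106 D + ½ × (1 + r) × D × 12/52.
- Ratio of the two = 1 + (12/11) × (1 + r) / 1, with the common factor ½ × D/52 cancelled.

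**Results**

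| Share of D left at week 23 | QALY gain to week 23 | Week 23 / week 11 | Share captured at week 11 |
|---|---|---|---|
| r = 1 | 0.337 D | 3.18 | 31% |
| r = 0.5 | 0.279 D | 2.64 | 38% |
| r = 0 | 0.221 D | 2.09 | 48% |

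As an illustration with an assumed D = 0.05, the gain is 0.0053 QALYs to week 11. To week 23 it is 0.0168 if kept (0.05 × 0.337) and 0.0111 if faded to zero (0.05 × 0.221). Changing D rescales these figures but not the ratios; the assumption that matters is r.

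**From QALYs to cost per QALY.** In the payer perspective the incremental cost is essentially the same at both horizons, so the cost per QALY moves in inverse proportion to the gain. The week-11 figure is about 2.1 to 3.2 times the week-23 figure.

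**Where the multiple does not carry over**
- *Healthcare and societal perspectives.* Costs measured by TIC-P continue after week 11. The incremental cost to week 23 may be higher or lower than to week 11, so neither the size nor the direction of the change in cost per QALY can be derived.
- *Responder-based analysis.* Responder status is read at one time and does not accumulate. A short horizon leaves out durability and later costs there, but not accrued benefit.

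**The case against.** The strongest reply is that week 11 is a deliberate and consistent choice. The Introduction lists cost-effectiveness among the week-11 secondary aims, section 2.8 follows it, and the horizon matches the primary endpoint. A week-11 ratio is a valid figure for its stated horizon, and the article does not rule out further analyses. This stands: there is no contradiction in the document.

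A reader might infer more than the article supports:

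- *That the week-11 cost per QALY is wrong, or several times too high.* It is high only relative to a longer horizon, and a multiple of about 3.2 requires the gain to be kept in full to week 23.
- *That the fourth aim goes unanswered.* That aim states no horizon, and section 2.8 delivers all three of its perspectives. It is answered for a short period.
- *That week 23 must replace week 11, for the responder analysis as well.* The accrual argument does not reach the responder analysis. Demoting a stated horizon is also hard to justify when 87 of 110 participants were already included at submission.

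Two further cautions hold. Participants who start other treatment are not automatically discontinued (section 4), so the arms are free of trial-offered I-BT until week 23 but not of all other treatment. And the article does not give the TIC-P recall period, so it is not certain that the week-23 questionnaire covers all of weeks 11 to 23.

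The objection that persistence is only assumed carries less weight. Persistence is the trial's own hypothesis, and even linear fading to zero by week 23 leaves about half of the gain outside the week-11 count.

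**Conclusion.** The point holds as a cheap improvement, not as an error. For the payer-perspective cost-utility analysis, one of six planned combinations (two analyses by three perspectives), the week-11 horizon sets essentially all of the intervention cost against roughly a third to a half of the QALY gain that the trial can observe before controls are offered I-BT. This rests on the linear rise to week 11, on persistence between none and full at week 23, and on negligible intervention cost after week 11. For the other two perspectives the case is only that available week-23 data on both costs and utilities would otherwise go unused in the economic evaluation as described.

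**What to change.** Keep the planned week-11 analyses and pre-specify beside them a between-arm cost-utility analysis to week 23:

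- QALYs as the area under the AQoL-6D utility curve from baseline, week 11 and week 23, with the arm difference adjusted for baseline utility.
- Intervention costs plus TIC-P costs cumulated to week 23, provided that the TIC-P recall period covers weeks 11 to 23. State that period.
- A sentence noting that the week-11 ratio covers a short horizon wherever it is compared with willingness to pay.

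Do not extend the randomised between-arm comparison to 14 months, because controls may have received I-BT by then.

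The data are already planned, so the cost is some extra analysis, somewhat more missing data at week 23, possible use of other treatments between weeks 11 and 23, and a protocol modification to be described publicly, as section 2.1 provides. Section 5 places the start of data analysis after the primary-endpoint data are complete in July 2025, so at submission the addition could still be made before results were seen.

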## Discussion

3

This will be the first superiority trial to compare a therapist-guided digital I-BT programme, primarily consisting of ERP, for adults with TS/CTD to an active control group. This trial aims to provide a population that rarely has access to effective treatments with an evidence-based intervention that can be widely disseminated.

## Ethics and dissemination

4

This study has been approved by the Swedish Ethical Review Authority (EPM 2023-06541-01). The benefits of the project outweigh its potential harms. The treatment is built on the same evidence-based principles shown to be safe in previous trials and in our own pilot trial (21). The participants in the control condition will have a chance to receive the treatment after the data from the first follow-up are collected. The participants’ symptoms will be closely monitored by the study personnel. At signs of deterioration or worsening of symptoms of depression or suicidal ideation, the participant will be assessed by a licensed clinical psychologist or psychiatrist. If necessary, the trial participation will be ended for these participants, and they will be referred to adequate medical services. All participant data will be collected and stored at either the encrypted treatment platform BASS4, run by the Karolinska Institutet eHealth Core Facility and requiring two-step authentication, or at the encrypted servers at Karolinska Institutet, set up specifically for storing sensitive research data and requiring a VPN-connection. There will be no external data monitoring committee in this trial. All data will be monitored in-house by study personnel. Participants always have the right to discontinue treatment at any time, without needing to provide an explanation. The research team is not allowed to modify the intervention, but the participants are not prohibited to do so, meaning their treatment will not be automatically discontinued if they engage in another treatment.

The publications within the current project will be published in Open Access journals. The statistical code for the analyses will be uploaded at osf.io (https://osf.io/cq97b/) and a detailed description of the dataset will be saved in Swedish National Database (SND).

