	Previous BT for TS/CTD of a minimum of 8 sessions with a qualified therapist within 12 months prior to assessment.^a^
	Adjustment of medication for TS/CTD within the last two months prior to assessment.^a^
	Severe psychiatric comorbidities such as organic brain disorders, bipolar disorder, ongoing psychosis, anorexia nervosa or substance use disorders that may interfere with the treatment for TS/CTD.^a^
	Acute psychiatric problems such as severe depression or suicidal risk needing immediate psychiatric care.
	Severe tics causing immediate risk to the participants themselves or to others and requiring urgent medical attention.

DSM-5, diagnostic and statistical manual of mental disorders, fifth edition; TS/CTD, Tourette syndrome/ chronic tic disorder; YGTSS, Yale Global Tic Severity Scale; YGTSS-TTS, Yale Global Tic Severity Scale—Total Tic Severity subscale.

^a^
These criteria are selected for exclusion as these factors can interfere with the treatment.

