The primary outcome measure will be the YGTSS-TTS (22), administered by a clinician blinded to the randomization condition. The raters will be psychiatrists or psychiatry residents, clinical psychologists, psychologists under training or psychology students receiving supervision. The raters will receive training in administering the YGTSS and participate in at least two test ratings with subsequent supervision before they are allowed to conduct assessments in the trial. Co-ratings will be arranged every 6 months for the active raters during the data collection period. Data on inter-rater reliability will be reported.

Secondary clinician-rated outcome measures will be the YGTSS-Impairment, as well as the Clinical Global Impression—Severity and Improvement (CGI-S and CGI-I, the latter not administered at pre-treatment) (23). The clinicians will receive training in administering the CGI that will be repeated every 6 months. Participants that are rated as “much improved” or “very much improved” on the CGI-I will be classified as treatment responders (24). If the participant keeps the responder status at subsequent follow-ups, they will be classified as long-term responders at that follow-up.

Self-rated tic-specific outcome measures will be the Adult Tic Questionnaire (ATQ) (also administered weekly) (25), the Gilles de la Tourette Syndrome—Quality of Life Scale (GTS-QoL) (26), and the Work and Social Adjustment Scale (WSAS) (27) adapted for TS/CTD by the research team. General quality of life will be measured using the Assessment of Quality of Life—6 Dimensions (AQoL-6D) (28), and these scores will be used in the health-utility analysis (see below). Symptoms of depression will be assessed using Montgomery-Asberg Depression Rating Scale—Self-report (MADRS-S) (29) (also administered at week 3 and 7). The self-reported Treatment Inventory of Costs in Patients with psychiatric disorders (TIC-P) will be administered to measure health-related costs (30).

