Negative effects will be assessed by administering a 16-item questionnaire on negative events developed by the research group at post-treatment and at week 23. Adverse events connected to worsened symptoms, suicidality, and impatient care will be measured using an additional questionnaire developed by the research group focusing specifically on whether those events have occurred, with possibility for elaboration, also administered at week 6. Spontaneously reported adverse events will be registered. Patient safety will be monitored during the recruitment procedures, by administering the MADRS and an adverse events questionnaire twice during the treatment, as well as by clinician monitoring in their contact with the participants. In case of significant deterioration, severe depressive symptoms or signs of suicidality, or in case of progression of other psychiatric disorder needing medical attention, the participant will be contacted for an additional assessment and an experienced clinician will decide on recommended future care (e. g., discontinuation of the treatment, referral to inpatient or other outpatient care).

To promote completion of follow up questionnaires, the participants will receive automatic reminders via text messages in the study platform. In case of longer measurement inactivity, study personnel will be contacting the participants via text messages or by phone.

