### Statistical methods

2.7

The significance level for all statistical tests will be *α* = 0.05. For all scale level measures, Cohen's d will be used as a measure of effect size. Odds ratios will be reported for categorical variables. Confidence intervals (95%) will be reported for all estimated measures.

The intention-to-treat approach to the analysis population will be applied in all cases unless specified otherwise. In case more than 10% of the data is missing, maximum likelihood imputations will be performed based on demographical data and the scores from the pretreatment assessment. The between-group differences at week 11 (primary endpoint) for the primary (YGTSS-TTS) and secondary outcome measures, an analysis of covariance (ANCOVA) with pre-score of the measure as covariate will be calculated. For ATQ and WSAS that are collected weekly, mixed effect models will be applied with random intercept and random slope. Chi squared tests will be calculated to explore the between-group differences in proportions of responders and long-term responders at all endpoints.

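### The ethics section lets trial participation, not only treatment, be ended for participants who deteriorate; followed as written, this can stop their later harms and depression assessments

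*Protocol article*

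**What the plan says.** Section 4 (Ethics and dissemination) of the protocol article provides that a participant with signs of deterioration, worsening depression or suicidal ideation is assessed by a licensed clinical psychologist or psychiatrist. It then says: "If necessary, the trial participation will be ended for these participants", with referral to medical services. The same section describes the participant's own right to stop as a right to discontinue treatment.

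Section 2.4 (Outcomes) covers nearly the same event and says that "an experienced clinician will decide on recommended future care (e. g., discontinuation of the treatment, referral to inpatient or other outpatient care". This is an open list of examples, and ending trial participation is not among them.

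Section 2.4 and Table 3 set the measures that bear on harm. There is "a 16-item questionnaire on negative events developed by the research group at post-treatment and at week 23", and an adverse-event questionnaire given during treatment and at weeks 11 and 23. The MADRS-S is given at the main time points and "also administered at week 3 and 7".

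On retention, section 2.4 provides automatic reminders, and adds: "In case of longer measurement inactivity, study personnel will be contacting the participants via text messages or by phone". Section 2.7 (Statistical methods) states: "The intention-to-treat approach to the analysis population will be applied in all cases unless specified otherwise". If more than 10% of the data is missing, "maximum likelihood imputations will be performed based on demographical data and the scores from the pretreatment assessment".

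**The concern.** Ending treatment and ending participation differ in their effect on the data. A participant who stops treatment can still be assessed. One whose participation has ended would ordinarily not be. The article does not say that participants removed for deterioration keep their week-11, week-23 or 14-month assessments, and the retention text deals with inactivity, not removal.

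The participants affected are chosen by a bad course, so the missing data would depend on outcome. They are the people for whom negative effects and depression most need recording. Their absence would make depression and later harms look somewhat better than they were. The trial also has no external data monitoring committee, so the harms record rests on in-house data.

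**Working it through.** The plan gives no removal rate and no figure on this point, so there is none to reproduce. The check has three parts: a count from the schedule, a reading of the analysis rules, and an illustration under stated assumptions.

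**1. What removal during treatment loses (section 2.4, Table 3)**

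| Measure | Scheduled after baseline | Lost if removed during treatment |
|---|---|---|
| Negative effects | weeks 11, 23 (2) | 2 of 2 |
| Adverse-event questionnaire | twice during treatment, weeks 11, 23 (4) | at least 2 of 4 |
| MADRS-S | weeks 3, 7, 11, 23, 14 months (5) | at least 3 of 5 |

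The minimum for MADRS-S applies to removal after week 7; removal before week 7 loses at least 4 of 5. The adverse-event count of four follows Table 3 and the statement that the questionnaire is given twice during treatment. The prose names week 6 as the in-treatment time.

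What is already recorded by then stays recorded: the in-treatment MADRS-S and adverse-event forms, spontaneous reports, and the weekly ATQ and WSAS.

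**2. Whether the analysis repairs the loss (section 2.7)**

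- Imputation starts only above 10% missing. Even 5 removals in each arm give (5 + 5) / 110 = 9.1%, so these removals alone would not start it.
- If it does start, it uses demographics and pre-treatment scores.
- If it does not, the week-11 ANCOVA adjusts for the pre-score only.

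On either route the week-3 and week-7 MADRS-S, which would show the worsening, do not inform the missing week-11 value.

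**3. Size of the effect on week-11 MADRS-S**

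From the documents: 110 randomised 1:1, so 55 per arm, and ANCOVA on the pre-score. Assumed: standardised normal scores with correlations pre/week 7 of 0.6, pre/week 11 of 0.5, and week 7/week 11 of 0.6 or 0.8; the k most extreme participants in an arm are removed; no treatment effect (an additive one does not change the bias). There were 4,000 simulated trials per setting.

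Model: week-11 score = a + b × arm + c × pre-score + error. Bias = mean of (estimate of b after removal − estimate of b with everyone). Arm-mean shift = mean of those kept − mean of all in the arm. Ranges run over the two week 7/week 11 correlations.

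| Removed | Between-arm bias, SD (highest week-7 scores removed) |
|---|---|
| 1+1 or 3+3 | about 0 |
| 2 vs 1, or 3 vs 2 | 0.01–0.02 |
| 1 of 55, one arm only | 0.013–0.021 |
| 3 of 55, one arm only | 0.035–0.057 |
| 5 of 55, one arm only | 0.056–0.092 |

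The stated trigger is worsening, so the run was repeated removing the largest week-7 minus pre-treatment changes. Between-arm bias is similar: 0.04–0.065 SD for 3 of 55 in one arm, and up to about 0.10 SD for 5 of 55. The improvement in an arm's own mean is 0.005–0.015 SD for 1 of 55 and about 0.01–0.04 SD for 3 of 55.

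Hand check of the upper figure: removing k of n people who average m SD worse than expected shifts the arm by k × m / (n − k). For k = 5 and n = 55 this is 5m / 50 = 0.1m. A bias of 0.10 SD therefore needs the five removed to average about 1 SD worse than their pre-scores predict.

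**4. Primary outcome (YGTSS-TTS)**

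Further assumptions: pre/post correlation 0.6, and mood–tic correlation 0.3 at the same stage and 0.21 between pre and later. With removal by highest week-7 MADRS-S, bias is under 0.01 SD if the arms differ by one, and 0.032 SD if 5 of 55 are removed from one arm only. That is 0.032 / 0.5 = 6% of the planning effect.

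**The case against.** The strongest reply is that the working safety procedure is in the Outcomes section, which speaks of treatment, and that the ethics section only summarises it. The step is conditional and follows clinical assessment. The article nowhere says that assessments stop, and a safety exit for a suicidal participant is legitimate. Follow-up after discontinuation is also a detail that an article may leave to the full protocol. Most of this stands as a reason for a low rating. It does not remove the point, because the ethics section is not silent: it names participation as what ends, and staff following it could stop assessments.

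It is also fair that the triggering event is largely recorded before removal, and that removals are probably few. Entry already excludes "Acute psychiatric problems such as severe depression or suicidal risk needing immediate psychiatric care".

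Four stronger readings are tempting and not supported:

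- A reader might infer that the two sections contradict each other, or that the rule breaks intention-to-treat. The Outcomes list is open-ended, and intention-to-treat is weakened by avoidable missing data, not contradicted.
- A reader might infer a bias favouring one arm. Scheduled monitoring is the same in both. Therapist contact is more active in the intervention arm, so detection could differ, but the documents do not settle the direction.
- A reader might model removal by the highest week-7 score and conclude that an arm's MADRS-S mean improves by 0.07–0.09 SD with 3 of 55 removed. The rule is triggered by worsening, which gives about 0.01–0.04 SD.
- A reader might infer a threat to the primary result. The figures above do not show one.

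**Conclusion.** The point holds as a wording inconsistency with a real but small consequence, and is worth correcting as a cheap improvement. The firm part is categorical and rests on the schedule alone: a participant whose participation is ended during treatment supplies no negative-effects questionnaire, and the planned analysis has no route by which in-treatment MADRS-S informs the missing week-11 value.

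The size on MADRS-S is illustrative. It depends on assumed correlations and assumed numbers removed, and taking exactly the most extreme participants is a worst case. A between-arm bias near 0.10 SD needs five removals in one arm and none in the other; near-balanced removals give 0 to 0.02 SD. Confidence is medium, mainly because the authors may have meant treatment only.

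**What to change.** Reword the sentence in section 4 along these lines: deterioration may end the study treatment and lead to referral at the clinician's discretion; the participant is still offered the week-11, week-23 and 14-month assessments and the safety questionnaires, unless they decline, withdraw consent, or the clinician judges contact unsafe. In the results, report by arm how many were discontinued for deterioration and how many of those were assessed afterwards.

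The cost is one sentence, posted by the route that section 2.1 sets for protocol modifications (osf.io and ClinicalTrials.gov), with a note to therapists and assessors. An ethics amendment may be needed. Data collection is already remote and staff already follow up inactive participants, so the added burden is a few contacts with unwell people. Sample size and clinical discretion are unchanged. With 87 of 110 included at submission, some treatment periods had already passed, but the last follow-up was planned for July 2026, so the change could still protect later assessments. If assessments already continue in practice, it only brings the text into line.
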